### Sample Size

LUCENT adopts a nonspecific sample size approach, allowing for the inclusion of eligible participants based on the defined criteria. The study aims to enroll a diverse and representative sample of lung cancer patients diagnosed in early and locally advanced stages to capture a comprehensive range of outcomes and experiences. Participants meeting the inclusion criteria will be recruited consecutively from participating institutions to ensure a systematic and unbiased selection process. The study will involve multiple centers across Italy to enhance the diversity and generalizability of the study findings. Data collection will be facilitated through a web-based registry developed for the study, allowing for standardized and centralized data collection from various participating sites.

### Recruitment

Recruitment involves the following:

Collaboration with health care institutions: Forge partnerships with a network of health care institutions across Italy.Multidisciplinary team engagement: Involve a multidisciplinary team, including thoracic surgeons, oncologists, and research staff, in the recruitment process.Patient advocacy groups: Partner with patient advocacy groups focused on lung cancer. Leverage these groups to disseminate information, support recruitment efforts, and enhance community trust.Continuous communication: Maintain open and continuous communication with potential participants throughout the recruitment period.Address concerns, provide clarifications, and emphasize the value of their contribution to research.Regular site meetings: Conduct regular meetings with site staff to share best practices, address challenges, and reinforce recruitment strategies. Foster a collaborative and motivated research team.

The study aims to achieve adequate participant enrollment by combining these strategies, ensuring a diverse and representative sample to meet the target sample size within the specified recruitment period.

### Assignment of Interventions: Allocation

Sequence generation, concealment mechanism, and implementation are not applicable as this is a nonrandomized observational study.

### Assignment of Interventions: Blinding

The blinding approach is as follows:

Participants: Owing to the nature of the surgical intervention, participants and those directly involved in their care can access the assigned intervention. It is challenging to blind participants and health care providers involved in surgical procedures.Care providers: Surgeons, health care providers, and clinical care teams responsible for delivering the interventions will not be blinded. Their awareness of the assigned surgical approach is essential for providing appropriate care.Outcome assessors: Outcome assessors will be blinded to the assigned interventions, particularly those collecting objective clinical data and endpoints. This includes individuals responsible for assessing recurrence rates, overall survival, and disease-free survival.Data analysts: Data analysts involved in the statistical analysis of study outcomes will be blinded to the assigned interventions. Blinding at this stage helps ensure unbiased data interpretation.Statistical team: The statistical team responsible for analyzing and interpreting the study results will conduct blinded analyses to prevent potential bias in reporting.Data monitors and auditors: To maintain objectivity, data and external auditors may also be blinded to treatment assignments during monitoring and auditing activities.

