### Additional Consent Provisions for the Collection and Use of Participant Data and Biological Specimens

We will conduct the trial according to the ICH Good Clinical Practice (GCP) guidelines. Accurate and consistent records are essential to a cooperative study.

The clinical and surgical data collected in a standardized endorsed data set can be downloaded locally and used for internal quality analyses or institutional research. The data collection methodology will use a website platform that meets international data privacy protection standards and rules. Notably, data are anonymously reported, independently accessed, and encrypted for other users.

For joining the database, the login of each institution will be provided after downloading and completing an application form from the project homepage and directly sending an email to the study coordinator. Investigators will access the patient medical records and enter the required data into the database. Protected health information will not be reused or disclosed to any other person or entity, except as required by law, for authorized research project oversight.

In compliance with the ICH-GCP guidelines, the investigator or institution will maintain all electronic case report forms, all source documents that support the data collected from each subject, all study documents as specified in ICH-GCP Section 8 (Essential Documents for the Conduct of a Clinical Trial), and all study documents as determined by the applicable regulatory requirements. The investigator or institution will take measures to prevent accidental or premature destruction of these documents. Essential documents must be retained until at least 25 years after the last approval of a marketing application in an ICH region and until there are no pending or contemplated marketing applications in an ICH region or until at least 15 years have elapsed since the formal discontinuation of clinical development of the investigational product. These documents will be retained longer if required by the applicable regulatory requirements or an agreement with the sponsor. The sponsor is responsible for informing the investigator or institution when these documents no longer need to be retained.

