### Procedure for Unblinding if Needed

Unblinding will only occur under predefined circumstances where knowledge of the treatment assignment is deemed crucial for participant safety or well-being. Only authorized personnel, such as a designated unblinding officer, will access confidential information regarding treatment assignment. The unblinding officer will be independent and not involved in the study’s day-to-day management or the participants’ direct care. The unblinding process will be secure, ensuring only authorized personnel can access information that reveals treatment assignment. Access to unblinded information will be password-protected and restricted to authorized individuals. The unblinding officer will maintain updated emergency contact information for each participant. In an emergency, the unblinding officer can quickly and efficiently communicate the relevant treatment assignment to the appropriate health care providers. All instances of unblinding, including the reason for unblinding, will be thoroughly documented. Documentation will include the date, time, individuals involved, and the specific circumstances necessitating unblinding. A clear communication plan will be established to ensure that unblinding occurs promptly and reaches the relevant individuals in emergencies. Records of unblinding events will be securely stored and kept separate from the primary study database. Access to these records will be restricted to authorized personnel and regulatory authorities, as necessary. Unblinding events and the reasons for unblinding will be promptly reported to the relevant ethical review boards and regulatory authorities. Following any unblinding event, the study team will reassess the blinding procedures to determine if modifications are needed to prevent similar situations in the future. Participants involved in an unblinding event will be promptly notified of the situation, and clear and accurate information about the intervention they received will be provided.

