### Data Collection and Management

The plans for the assessment and collection of outcomes are as follows:

Longitudinal clinical outcomes: Regarding assessment, long-term clinical outcomes, including recurrence rates, overall survival, and disease-free survival, will be assessed through regular follow-up visits and medical records review. Regarding collection, outcome assessors will collect data during scheduled follow-up visits, and data entry personnel will ensure accurate and timely recording in the study database.PROs: Regarding assessment, patient-reported well-being and quality of life outcomes will be assessed using online questionnaires. Regarding collection, participants will be provided access to secure online questionnaire-completion platforms. Data will be automatically recorded in the study database.Health care resource utilization: Regarding assessment, health care resource utilization, including hospital stay and postoperative care, will be assessed through medical records and billing data. Regarding collection, data collection personnel will extract relevant information from medical records, and billing data will be obtained and recorded for economic analyses.Treatment decision patterns: Regarding assessment, patterns in treatment decisions, considering tumor characteristics and patient preferences, will be assessed through medical records and clinician interviews. Regarding collection, data collection personnel will document treatment decisions in the study database based on comprehensive reviews of medical records.Economic and psychosocial impact: Regarding assessment, economic and psychosocial impact assessments will be conducted through standardized tools and interviews. Regarding collection, trained personnel will administer economic and psychosocial assessments, and the results will be recorded in the study database.AEs and complications: Regarding assessment, continuous monitoring and medical records review will assess AEs and complications. Regarding collection, data collection personnel and safety monitoring teams will document AEs and complications in the study database.Stratification factors: Regarding assessment, stratification factors, including tumor stage and patient demographics, will be assessed at baseline. Regarding collection, data collection personnel will collect baseline information during participant enrollment and document it in the study database.Data quality assurance: Regarding assessment, regular audits and validation checks will continuously monitor data quality. Regarding collection, data management personnel will conduct routine quality checks to ensure the accuracy and completeness of the collected data.Data security and confidentiality: Regarding assessment, data security and confidentiality measures will be assessed through regular reviews and audits. Regarding collection, data management personnel will implement encryption, access controls, and other security measures to protect participant information.Reporting and analysis: Regarding assessment, reporting and analysis plans will be periodically reviewed and updated as needed. Regarding collection, the statistical team will conduct blinded data analyses to generate reports for internal and external stakeholders.

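### The article claims blinded assessment of recurrence and survival, but its own data flow contradicts this and no masking step is described

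*Protocol article*

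**What the plan says.** The section Assignment of Interventions: Blinding makes an unqualified claim: "Outcome assessors will be blinded to the assigned interventions, particularly those collecting objective clinical data and endpoints". It then names the endpoints: "This includes individuals responsible for assessing recurrence rates, overall survival, and disease-free survival". In the same section, participants are described as able to know their operation, and "Surgeons, health care providers, and clinical care teams responsible for delivering the interventions will not be blinded". Data analysts and the statistical team are also said to be blinded.

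The next section, Procedure for Unblinding if Needed, treats the surgical approach as a secret to be guarded: "Unblinding will only occur under predefined circumstances where knowledge of the treatment assignment is deemed crucial for participant safety or well-being", and "Only authorized personnel, such as a designated unblinding officer, will access confidential information regarding treatment assignment".

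On conduct, Data Collection and Management says of recurrence and the two survival endpoints that they "will be assessed through regular follow-up visits and medical records review". The section on additional consent provisions says of registry data in general: "Investigators will access the patient medical records and enter the required data into the database".

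**The concern.** Comparing surgical approaches is a stated purpose of the study (Explanation for the Choice of Comparators; Intervention Description), and recurrence and disease-free survival are among its listed outcomes. When recurrence is called, and on what evidence, depends partly on judgement. If the person making the call knows the operation, expectation can enter. Masked assessment is the usual safeguard, and a reader who sees it claimed will discount that risk.

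If the claim cannot be met by the process described, later publications could report masked endpoint assessment that did not take place. Open ascertainment is also absent from the limitations listed in the Discussion, so nothing in the article corrects the impression.

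**Working it through.** No arithmetic applies. The article gives no event count, power or effect size on which the point depends. The check sets the statements side by side.

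1. **Where the outcomes come from.** Recurrence, overall survival and disease-free survival come from follow-up visits and records review (Data Collection and Management). The patients at those visits know their operation (Blinding section).

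2. **Who handles them.** Data Collection and Management names outcome assessors, who collect at visits, and data entry personnel, who record. The consent-provisions section has investigators reading the records and entering the data. Whichever role does the work, the source is an unblinded patient or a medical record.

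3. **Whether that source shows the approach.** The article does not say in so many words that the record states the operation. It follows from two other statements. Treatment decisions are documented from review of medical records (Data Collection and Management). Intervention, perioperative and postoperative data all go into one registry (Intervention Description).

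4. **Whether a masking step is described.** None is: there is no redaction of records, no masked registry view and no independent adjudication of recurrence. The Confidentiality section provides role-based, least-privilege access to data sets. It does not link this to surgical approach, and it would not mask the medical record itself.

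5. **Whether there is anything to unblind.** The allocation section says that concealment does not apply because the study is nonrandomized and observational. The unblinding section nevertheless says that in an emergency "the unblinding officer can quickly and efficiently communicate the relevant treatment assignment to the appropriate health care providers". The Blinding section says that those providers already know the approach. The unblinding section also promises to tell participants which intervention they received, although they too can already know it. The procedure would disclose known information to people who hold it.

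6. **Analysts.** Coded approach labels could mask an analyst. However, Dissemination Plans has the principal investigators perform the final analysis, and the section on discontinuing or modifying interventions involves the principal investigator in decisions to change a participant's intervention. The analyst-blinding statement therefore also needs reconciling.

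7. **Which outcomes are exposed.**
   - Recurrence: exposed, because ascertainment involves judgement.
   - Disease-free survival: exposed through its recurrence component. Deaths counted in it are not.
   - Overall survival: little exposed.
   - Comparison of centres with national benchmarks, including length of stay (the article's own example): largely unaffected, since masking to approach does not bear on it.

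**The case against.** The strongest reply is that this is a journal article. A masking procedure is the kind of detail a full protocol holds, and the full protocol is not shown. Outcome assessors are named as a role apart from care providers, and role-based access could support a masked view of the registry. The endpoints concerned are listed as additional outcomes, not as the primary objective.

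Much of this stands. The absence of a described mechanism would not by itself be a finding, and the placing of these endpoints limits the consequence. What remains is that the article states a property and then describes a process that contradicts it, and that the unblinding section conflicts with the two sections before it. Naming separate assessors does not remove this, because they work from the same visits and records.

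A reader might infer more, and the documents do not support it:
- That masking cannot exist anywhere. Only the contradiction in the text shown is established.
- That the same people enter both the approach and the outcome. Overlap of roles at a site is not stated.
- That lack of funding rules out an adjudicator. The Discussion mentions the absence of external funding in general and says nothing about assessors.
- That the claim is also false for patient-reported outcomes. The article makes no masking claim for them, and participants are expressly unblinded.
- That the bias would favour the newer technique. The article describes expected benefits of minimally invasive surgery, but the direction of any ascertainment bias would be an assumption.

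**Conclusion.** The point holds in a limited form. The claim that assessors of recurrence, overall survival and disease-free survival are blinded is contradicted by the data flow the article describes, and no mechanism is given that would make it true. The unblinding procedure has no function in this design.

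The reach is comparisons of surgical approach on recurrence and on the recurrence component of disease-free survival. These outcomes are open to possible bias; that does not mean that every event is biased, and no size or direction can be derived. The conclusion rests on one inference, that the medical records reviewed for outcomes reveal the operation. The article's own use of medical records to document treatment decisions makes that inference reasonable. The correction should be made, because it changes the risk-of-bias statement for those comparisons. It does not undermine the primary objective.

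**What to change.** - In Assignment of Interventions: Blinding, withdraw the outcome-assessor claim and state that ascertainment is open.
- Delete Procedure for Unblinding if Needed, or reconcile it with the allocation and blinding sections.
- Anchor recurrence to the date of the first positive imaging or pathology report, so that the event rests on a dated document.
- Add open ascertainment to the limitations in the Discussion, for comparisons of approach on recurrence and disease-free survival.
- Keep only analyst masking, by coded approach labels, and reconcile it with Dissemination Plans, where the principal investigators perform the final analysis.

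There is no need to make all-cause mortality the lead long-term endpoint. That would be a preference about endpoints, and the contradiction does not require it.

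The cost is mostly wording, plus a recurrence date rule in the registry. The downside is a less favourable but accurate statement on risk of bias.

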### Procedure for Unblinding if Needed

Unblinding will only occur under predefined circumstances where knowledge of the treatment assignment is deemed crucial for participant safety or well-being. Only authorized personnel, such as a designated unblinding officer, will access confidential information regarding treatment assignment. The unblinding officer will be independent and not involved in the study’s day-to-day management or the participants’ direct care. The unblinding process will be secure, ensuring only authorized personnel can access information that reveals treatment assignment. Access to unblinded information will be password-protected and restricted to authorized individuals. The unblinding officer will maintain updated emergency contact information for each participant. In an emergency, the unblinding officer can quickly and efficiently communicate the relevant treatment assignment to the appropriate health care providers. All instances of unblinding, including the reason for unblinding, will be thoroughly documented. Documentation will include the date, time, individuals involved, and the specific circumstances necessitating unblinding. A clear communication plan will be established to ensure that unblinding occurs promptly and reaches the relevant individuals in emergencies. Records of unblinding events will be securely stored and kept separate from the primary study database. Access to these records will be restricted to authorized personnel and regulatory authorities, as necessary. Unblinding events and the reasons for unblinding will be promptly reported to the relevant ethical review boards and regulatory authorities. Following any unblinding event, the study team will reassess the blinding procedures to determine if modifications are needed to prevent similar situations in the future. Participants involved in an unblinding event will be promptly notified of the situation, and clear and accurate information about the intervention they received will be provided.

### Data Collection and Management

The plans for the assessment and collection of outcomes are as follows:

Longitudinal clinical outcomes: Regarding assessment, long-term clinical outcomes, including recurrence rates, overall survival, and disease-free survival, will be assessed through regular follow-up visits and medical records review. Regarding collection, outcome assessors will collect data during scheduled follow-up visits, and data entry personnel will ensure accurate and timely recording in the study database.PROs: Regarding assessment, patient-reported well-being and quality of life outcomes will be assessed using online questionnaires. Regarding collection, participants will be provided access to secure online questionnaire-completion platforms. Data will be automatically recorded in the study database.Health care resource utilization: Regarding assessment, health care resource utilization, including hospital stay and postoperative care, will be assessed through medical records and billing data. Regarding collection, data collection personnel will extract relevant information from medical records, and billing data will be obtained and recorded for economic analyses.Treatment decision patterns: Regarding assessment, patterns in treatment decisions, considering tumor characteristics and patient preferences, will be assessed through medical records and clinician interviews. Regarding collection, data collection personnel will document treatment decisions in the study database based on comprehensive reviews of medical records.Economic and psychosocial impact: Regarding assessment, economic and psychosocial impact assessments will be conducted through standardized tools and interviews. Regarding collection, trained personnel will administer economic and psychosocial assessments, and the results will be recorded in the study database.AEs and complications: Regarding assessment, continuous monitoring and medical records review will assess AEs and complications. Regarding collection, data collection personnel and safety monitoring teams will document AEs and complications in the study database.Stratification factors: Regarding assessment, stratification factors, including tumor stage and patient demographics, will be assessed at baseline. Regarding collection, data collection personnel will collect baseline information during participant enrollment and document it in the study database.Data quality assurance: Regarding assessment, regular audits and validation checks will continuously monitor data quality. Regarding collection, data management personnel will conduct routine quality checks to ensure the accuracy and completeness of the collected data.Data security and confidentiality: Regarding assessment, data security and confidentiality measures will be assessed through regular reviews and audits. Regarding collection, data management personnel will implement encryption, access controls, and other security measures to protect participant information.Reporting and analysis: Regarding assessment, reporting and analysis plans will be periodically reviewed and updated as needed. Regarding collection, the statistical team will conduct blinded data analyses to generate reports for internal and external stakeholders.

The plans to promote participant retention and completion of follow-up are as follows:

Participant engagement initiatives: Implement a comprehensive plan to maintain ongoing communication and involvement. Regularly update participants on the study progress, key findings, and importance of their continued participation.Clear communication of study benefits: Communicate the potential benefits of the study to participants. Emphasize the contribution of their data in advancing scientific knowledge and improving lung cancer treatment strategies.Educational materials: Develop and distribute educational materials explaining the importance of follow-up assessments. Provide resources that enhance participants’ understanding of the study’s objectives and their role in contributing to research.Participant reminders: Implement a system of reminders for upcoming follow-up visits, assessments, and questionnaire completions. Use multiple communication channels, including emails, phone calls, and text messages, to ensure participants are aware of and prepared for scheduled activities.Flexible follow-up options: Offer flexible options for follow-up assessments, including virtual visits or alternative locations. Accommodate participant preferences to reduce barriers to attendance.Incentives for follow-up: Provide reasonable incentives for participants to complete follow-up assessments. Ensure that incentives comply with ethical guidelines and do not compromise the voluntary nature of participation.Dedicated study coordinator: Study coordinators will be a consistent point of contact, addressing participant queries and concerns.Continuous feedback loop: Establish a constant loop by soliciting participant feedback on their experiences.

